## Abstract

**Background:**

Most antibiotic prescriptions for acute cough due to lower respiratory tract infections (LRTI) in primary care are not warranted. Diagnostic uncertainty and patient expectations and worries are major drivers of unnecessary antibiotic prescribing. A C-reactive protein (CRP) point of care test may help GPs to better guide antibiotic treatment by ruling out pneumonia in cases of low test results. Alternatively, enhanced communication skills training to help clinicians address patients' expectations and worries could lead to a decrease in antibiotic prescribing, without compromising clinical recovery, while enhancing patient enablement. The aim of this paper is to describe the design and methods of a study to assess two interventions for improving LRTI management in general practice.

**Methods/Design:**

This cluster randomised controlled, factorial trial will introduce two interventions in general practice; point of care CRP testing and enhanced communication skills training for LRTI. Twenty general practices with two participating GPs per practice will recruit 400 patients with LRTI during two winter periods. Patients will be followed up for at least 28 days. The primary outcome measure is the antibiotic prescribing rate. Secondary outcomes are clinical recovery, cost-effectiveness, use of other diagnostic tests and medical services (including reconsultation), and patient enablement.

**Discussion:**

This trial is the first cluster randomised trial to evaluate the influence of point of care CRP testing in the hands of the general practitioner and enhanced communication skills, on the management of LRTI in primary care. The pragmatic nature of the study, which leaves treatment decisions up to the responsible clinicians, will enhance the applicability and generalisability of findings. The factorial design will allow conclusion to be made about the value of CRP testing on its own, communication skills training on its own, and the two combined. Evaluating a biomedical and communication based intervention ('hard' and 'soft' technologies) together in this way makes this trial unique in its field.

## Background

This article describes the design of a cluster randomised clinical trial (RCT) evaluating the clinical efficacy and cost-effectiveness of a point of care C-reactive protein (CRP) test and enhanced communication skills in the management of lower respiratory tract infections (LRTI) in general practice.

About 80% of all antimicrobials are prescribed in primary care, and up to 80% of these are for respiratory tract indications, including acute cough. Respiratory tract infections are by far the most common cause of cough in primary care[1,2]. Broad spectrum antibiotics are often prescribed for cough, including acute bronchitis[3,4], and many of these prescriptions will benefit patients only marginally if at all (Number Needed to Treat = 17)[5], and may cause side effects (Number Needed to Harm = 33)[5]. Unnecessary prescribing, especially of broad spectrum antibiotics, drives antimicrobial resistance, wastes money and raises wrong expectations for patients. Microbial resistance topped the list of priority intervention needs in the World Health Organization report on Priority Medicines. Although the Netherlands is one of the lowest antibiotic prescribing countries worldwide, unnecessary prescribing for LRTI remains of great concern[6]. While unnecessary prescribing is a highly complex phenomenon, much of it relates to two factors, diagnostic uncertainty and patients' expectations. Interventions therefore should be aimed at clinicians to address these two factors. Previous studies with interventions aimed at general practitioners have resulted in less antibiotic prescribing[7,8].

### Diagnostic uncertainty and C-Reactive protein

LRTI represents a source of considerable diagnostic uncertainty for clinicians. Only a small number of patients with signs and symptoms of LRTI have pneumonia. Differentiating pneumonia from acute bronchitis on clinical grounds is often impossible and so clinicians frequently prescribe antibiotics empirically. However, as acute bronchitis is generally self-limiting, and benefits do not generally outweigh possible side effects from antibiotic treatment[5,9], rapid diagnostic tools to determine which patients will benefit from antibiotic treatment are urgently needed[10].

C-reactive protein is a marker of an acute inflammatory response. Several studies have indicated that CRP is probably the most feasible and accurate investigation to differentiate pneumonia from acute bronchitis in patients with LRTI in general practice [11-14]. We demonstrated in an earlier diagnostic study that for patients with a CRP less than 20 mg/l and who had no more than 1 of the 3 clinical predictors of pneumonia (dry cough, fever, diarrhoea), the absolute risk of pneumonia was reduced from 13% to less than 3%[11]. In daily practice a CRP value will only be useful when available during the initial consultation. CRP is available as a feasible point of care test for primary care and the test result can be available within three minutes. A low CRP test result is especially useful for reassuring both the doctor and the patient that further diagnostic testing and antibiotic treatment are not necessary. CRP tests can be done quickly, cheaply and with good reliability in everyday general practice using a finger prick blood sample[15]. In Scandinavia, point of care CRP testing is part of the routine evaluation of patients with LRTI in general practice, and its use has proved cost-effective[16,17]. In other countries including the Netherlands, however, GPs are still relatively unfamiliar with point of care CRP testing. The widespread introduction of point of care CRP testing in the Scandinavian countries was not accompanied by appropriate training for clinicians. This has led to an overuse of CRP testing in often mild respiratory tract infections. Slightly elevated CRP levels were too often followed by an unnecessary antibiotic course[18]. Therefore, thorough training in use and interpretation of test results is needed for a fair chance of success. This should include information about the diagnostic value of the test in addition to a focus on the fact that pneumonia can be excluded by a low test result.

### Patient expectations and enhanced communication within the consultation

Apart from diagnostic uncertainty, a range of other, 'non medical' influences come to bear on the decision to prescribe antibiotics[19]. Perceived patient pressure for an antibiotic, patient expectations and satisfaction are major factors influencing the decision whether to prescribe antibiotics [20-25]. Therefore, GPs need adequate communication skills to efficiently explain the pros and cons of antibiotic treatment, natural course and when to re-consult for this condition. Training GPs in enhanced consultations may therefore lead to easier and more acceptable non-antibiotic management[26]. Clinicians' communication skills in managing common infections are often sub-optimal[27,28]. In one of our studies, for example, carers' views/expectations on antibiotic treatment were elicited in only one of 39 audio taped consultations for children with respiratory tract infections[28]. Many GPs therefore do not routinely use optimal communication skills to efficiently implement a non-antibiotic management strategy that patients would find acceptable and is time efficient in time pressured consultations[29]. Although GPs perceive high patient expectations for antibiotics, evidence suggests that GPs are not good at estimating which patients expect antibiotics. Patient satisfaction is determined more by the quality of explanation and physical examination than whether or not they receive a prescription for an antibiotic[20,30]. Rollnick et al. developed an innovative communication skills training method which proved to be practical and acceptable to experienced clinicians[26]. With everyday clinical experience in the foreground and communication skills in the background this context-bound method proved successful in sore throat consultations and was well received by GPs[31]. We have shown that training clinicians using these methods was associated with changes in the behavior of clinicians and patients in consultations for common infections. In an interrupted time series pilot study, before training in our enhanced consultation skills, GPs in 10 consultations elicited patients concerns on two occasions and empathized three times in total[31]. No evidence was found of eliciting expectations of the consultation in general, or about antibiotics. After training, the same clinicians elicited patients concerns in 14 out of 15 consultations, elicited general expectations 8 times, elicited expectations about antibiotics in all 15 consultations, and empathized a total of 38 times. Before clinician training, patients expressed their expectations only once in 10 consultations and asked questions a total of 12 times. After clinician training, patients expressed expectations in 14 out of 15 consultations and asked questions a total of 33 times. Although the importance of studying an intervention like this in a large trial is obvious[32], as far as we know a full cost-effectiveness analysis has never been performed, to evaluate the efficacy of any intervention to improve health care providers' behaviour regarding antibiotics prescribing.

### Opportunities in LRTI

These studies on the potential for CRP and enhanced communication skills indicate that these interventions, either separately or combined, are able to have a positive effect on the prevention of misuse of antibiotics in LRTI. No point of care test has been evaluated together with context-bound training in enhanced communication skills.

Effective management of LRTI, we hypothesize, will involve a point of care test that performs well in primary care. It will also involve providing clinicians with the skills to efficiently and effectively communicate about the condition, its duration and implications to patients in a way that might make them accept a potential non-antibiotic management and facilitate patient enablement. However, some may argue that one of these interventions alone or indeed both together is required to enhance care. The factorial design of this study allows us to answer these questions.

### Research questions and outcome measures

This study will investigate the following research questions:

To what extent does the introduction of the C-Reactive Protein (CRP) point of care test and enhanced communication skills for managing LRTI in general practice, either separately or combined, have effect on:

#### Primary outcome measure

1. Immediate antibiotic prescribing rates

#### Secondary outcome measures

1. Clinical recovery and return to usual activities

2. Cost-effectiveness of point of care CRP and communication training

3. Patient enablement, satisfaction and future consulting intention

4. Diagnostic testing other than point of care CRP

5. Use of health services, including re-consultation

6. Subsequent antibiotic prescribing rates within 28 days of the initial consultation

### Ethical approval

The Ethics Committee of Catharina Hospital in Eindhoven, the Netherlands, approved the study protocol under number M05-1529, in compliance with the Helsinki Declaration.

## Methods/Design

This study is an open randomised controlled trial in general practice with randomisation at the practice level. The practices will be allocated to one of four groups (table 1):

**Table 1 T1:** Intervention allocation

		**Communication skills training**	
		**+**	**-**
**C-reactive protein point of care test**	**+**	5 practices (10 GPs)	5 practices (10 GPs)
		100 patients	100 patients
	**-**	5 practices (10 GPs)	5 practices (10 GPs)
		100 patients	100 patients

1. Access to and training in point of care CRP

2. Context-bound training in enhanced communication skills for acute cough

3. Access to and training in the use of point of care CRP plus context-bound training in enhanced communication skills for acute cough

4. Usual care.

The GPs in groups 1 and 3 will be trained to use and interpret point of care CRP and those in 2 and 3 in enhanced communication with patients.

### Randomisation

A cluster randomised design has been chosen to avoid contamination. In order to allow assessment of the effects of each individual intervention and of combinations of interventions, compared with a control group, a factorial design for randomisation by practice will be used. Two randomisation procedures will be undertaken, one to create two groups for CRP/no CRP and a second for communication skills training/No communication skills training. The process will be stratified by the classification of the practices as above/below average for their ability to recruit patients (total number of practitioner clinics per practice per week). This will ensure a balance in recruitment potential between the two arms. Random permuted blocks of four will be generated for each randomization process. This will create two groups of 10 practices and balance at the margins for the stratification variable.

### Sample size calculation

In order to detect a reduction in antibiotic prescribing from 80% to 60%, with 80% power at a 5% significance level, an individually randomised study would require 175 patients. If we randomise 20 practices with an intra-cluster correlation coefficient (icc) of 0.06 this increases to 350 patients. In order to allow for a 90% follow-up rate for the primary outcome measure of antibiotic prescribing we intend to recruit 400 patients (20 per practice and 100 in each cell). We have previously demonstrated that 40 GPs can recruit over 400 patients suspected of having a LRTI in two winter seasons[11].

### General practices

A total of 20 general practices will be recruited, with a fixed number of two GPs per practice participating in the study. The practices are located in the South-eastern part of the province of Noord-Brabant in the Netherlands. This region compromises both urban and rural areas. Recruited practices will be geographically spread throughout this region.

### Patients

The GPs will approach sequential eligible adult patients during regular consultation hours. Patients are eligible if they present in general practice with an acute cough, lasting no more than 4 weeks, considered to be caused by LRTI according to the GP. In addition, the patient needs to have at least one focal and one systemic sign/symptom[33] (Figure 1). Children will not eligible, since the diagnostic value of CRP has not been investigated for LRTI in children, consultations with children and their parents will be different with respect to communication styles and strategies, and diagnostic and prognostic factors are not automatically applicable in infants. Exclusion criteria are described in figure 1.

**Figure 1 F1:**
[figure not shown]
Study flow chart.

### CRP point of care test

20 GPs will have a CRP test device in their practice. CRP analysis will be carried out during the consultation. The NycoCard^® ^II Reader, product of Axis-Shield, will be used, in accordance with the manufacturer's instructions. The test system is based on an immunometric principle and consists of 1) a liquid for sample dilution and lysis of cells, 2) a test card with CRP-specific monoclonal antibodies coated to a membrane, 3) a conjugate solution with monoclonal antibodies coupled to ultra small gold particles and 4) a washing solution. One single drop of blood from a finger prick is needed to perform the test. A capillary collects 5 μl blood which is diluted in the 0,4 ml dilution liquid. 50 μl of this diluted sample is applied to the test well of the device. When the sample flows through the antibody-coated membrane, C-reactive proteins are forced to react and bind to the antibodies on the membrane. CRP trapped on the membrane will bind the antibody gold conjugate. Unbound conjugate is removed by one drop of washing solution. In the presence of pathological levels of CRP in the sample, the membrane appears red-brown with color intensity proportionally to the CRP concentration. The color intensity is measured quantitatively with the color densitometer NycoCard^® ^Reader II. The measuring range for whole blood samples is 8 to 250 mg/l. In the measuring range the test response is directly proportional to the concentration of CRP in the sample. For internal quality a control positive will be measured to confirm the efficacy and correct performance of the test. The control liquid is supplied with every test kit and will be run after opening of a new kit, which is once in every 24 regular tests. CRP measurements with Nycocard^® ^have proven to be valid and robust in general practice[34]. The result will be available within three minutes. This means that GPs can use the test result within the consultation. The 20 GPs who are allocated to the CRP intervention will be given guidance about the interpretation of CRP results. This information will include a comprehensive summary of the literature on LRTI and the role of CRP. We will not instruct the GPs in a prescription style fashion. Focus will be on informing them on the additional diagnostic value of CRP in ruling out pneumonia. GPs will decide on management including possible antibiotic treatment in every patient. CRP may complement their clinical findings and help in deciding upon diagnosis and treatment. The desk reminder for CRP interpretation in LRTI can be seen in figure 2. Practice assistants will be trained to use the NycoCard^® ^II Reader by the Dutch distributor who has over 10 years of training experience. GPs and assistants will be able to consult a 24-hour helpdesk for technical assistance. Questions on interpretive issues can be submitted to the research team. For specific test handling questions, we will also create a direct telephone number connecting the assistant with a clinic where assistants have extensive experience with handling point of care CRP testing. Once the CRP devices have been installed and training sessions have been performed, practices will get a 8-week run-in period before inclusion starts for familiarisation with the device and interpretation of the results.

**Figure 2 F2:**
[figure not shown]
Desk reminders for GPs allocated to the CRP and/or communication skills interventions.

### Communication training

The communication training is based upon a patient-centred strategy to achieve shared decisions about investigation and treatment of acute infections. The intervention is based on the elicit-provide-elicit framework, which has its background in motivational interviewing and which has been refined for use in primary care[26]. The context-bound training for acquiring these communicating skills involves one two-hour training seminar at a central location, preceded and followed by consulting with simulated patients in routine surgeries. It involves the following specific elements:

#### 1. Simulated patient in clinical encounter, part 1

Two experienced simulated patients will be trained to simulate a patient with acute bronchitis persisting for two weeks. The patient is worried about the duration of the cough and has distinct sleeping problems and impaired daily activities due to the cough. The simulated patients will consult with participating GPs at their own surgeries during regular surgery hours. The simulated patients will carry an audiotape device to record the conversation, which will be transcribed by trained typists.

#### 2. Seminar on shared decision making

Within one week after their first simulated patient consultation, all 20 GPs will gather for a training seminar on enhanced communication skills. Three seminars will be held, with 5–8 GPs participating per session. All session will have the same format and content (see below). An experienced moderator from the Department of Vocational Training in General Practice will lead the seminar. The GPs will be encouraged to actively participate in all sections of the training. After a brief introduction, the GPs will receive transcripts of their first simulated patient contact. They will be asked to read their own transcript and make notes. Subsequently, the moderator will invite them to share their reactions to their transcripts and to identify noteworthy aspects. These can be of any kind; structure, vocabulary or occurring difficulties in management. The focus will be on the acute cough patient. This will be followed by a short presentation on current views and insights on LRTI. The contrast between evidence from research and figures from daily practice will be highlighted to stress the importance of enhancing LRTI consultations. GPs will be given the opportunity to contribute their own suggestions for enhancing LRTI consultations. The elicit-provide-elicit framework will be outlined[26], where the GP first *elicits *what the patient knows about his condition and what the patient's main worries and expectations are. Crucially, the GP actively asks how the patient feels about antibiotics. This serves two purposes; firstly, to provide the GP with the patient's expectation and hope for antimicrobial treatment (making patients' expectations explicit). Secondly, it enables the GP to openly discuss his opinion on antibiotic treatment, mentioning the balance of possible benefits and harms of antibiotic treatment. Secondly, the GP *provides *information relevant to the patients' individual understanding and interest. This includes findings from the medical history and physical examination. Then the GP *elicits *the patients' interpretation about what has been said and done, and discusses implications for help seeking behaviour. Specific alarm symptoms should be mentioned to provide exact information to the patient about when to re-consult. All communication is based on an assessment of patients' information needs, thus achieving efficiency by targeting information to individual needs. Practice-based examples will be presented in video clips. Finally, GPs will be asked to attempt to identify the specific aspects, which need most attention during their consultations. Supported by a desk reminder (Figure 2) we will ask the GPs to implement the specific steps of the communication training in their routine acute cough consultations.

#### 3. Simulated patient in clinical encounter, part 2

The GPs will get the opportunity to use the enhanced communication skills in daily practice during eight weeks before inclusion start. The two simulated patients will now switch practices, visiting the practices they did not visit, while playing a similar acute bronchitis role. Trained typists will once again transcribe the audio-recorded consultations. These transcripts will be copied and made anonymous, after which they are sent to a colleague participating in the study. This GP will be asked to write comments on the transcript based on the enhanced communication method and to add possible suggestions for improvement. The project team will edit or add comments if needed. Finally, the peer-reviewed transcript will be returned to the GP who conducted the consultation. Commenting on a colleague's transcript may promote GPs' critical reflection on their own peer-reviewed transcripts. Thus, participating GPs will benefit from reading and feeding on a colleague's transcript and from reflection on their own transcript.

### Data collection

Sequential elegible patients will be asked by their GP to participate. During this consultation, the GP will take written consent and note the inclusion criteria on the trial inclusion form. The practice nurse will give each participant a simple self-complete symptom diary after the consultation. After general questions on cough and the consultation, patients will be asked each day to complete a 6 item scale, with responses to statements ranging from 0 to 6. A total symptom score will be derived from this scale. Items relate to coughing, phlegm, shortness of breath, sleep disturbance, impairment of normal daily activities, and generally feeling unwell. This symptom diary has previously been used in a large LRTI study[35]. Patients will then be followed-up for 28 days, or if still unwell, until recovered with a maximum follow up of ten weeks. Furthermore, weekly questions will record time off work, medication use and re-consultation. The recruiting GP will fax the informed consent form and inclusion form to the research team in Maastricht on the day of inclusion. The clinical effectiveness analysis will be based on diary responses. A single Likert type scale response item will assess satisfaction with the consultation. Patient enablement will be measured using the Patient Enablement Instrument [36] translated into Dutch. Concurrent validation will be undertaken. In addition, the research team will retrieve data on diagnosis, antibiotic prescription, re-consultation, diagnostic testing other than CRP and related medical consumption from participating patients' electronic medical records over 28 days follow-up. A societal perspective will be used for the economic evaluation. Thus, for all four groups, in addition to costs to the health care system, we will take into account medical costs borne by patients and production costs due to illness related absence from work. Use of health care facilities will be prospectively recorded in a standardised way including all re-consultations, telephone consultations, out-of-hours consultations, and hospital admissions, (repeat) prescription of antibiotics (type, dosage, duration) and additional diagnostic tests, including bacteriological culture and X-ray. A patient diary will be the basis for assessing actual medication use, other medical costs to the patient, and absence from work[37].

The research team will retain transcripts of simulated patient consultations. Transcripts before the seminar will be compared with those afterwards for evidence of acquisition of the enhanced communication skills (competence).

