### Analysis

Statistical analyses will be performed with the aid of the SPSS and STATA statistical packages. The primary analysis will be intention to treat and will compare the marginal effects of the two interventions on antibiotic prescribing at the index consultation and incorporate an interaction effect. The interaction term will be included to test for a synergistic or antagonistic relationship between the two interventions. This will be tested using a three level logistic regression model to account for variation at the practice/GP/patient. If there is no indication of random effects at a GP level, then this will be reduced to a two level model with GP seen acting as a patient level covariate.

A four level linear regression model will be fitted to the symptom scores (logged) to account for practice, GP, patient and repeated assessments over time. The correlation between repeated assessments within individual patients will be modelled to allow for greater correlation between assessments, which are closer in time. The effect of interventions would be seen in the comparison of the slopes of symptom scores over time in the groups, i.e. having faster (or slower) recovery rates[38]. Sensitivity analyses on the symptom scores will be undertaken to assess the impact of loss to follow-up by either interpolating from available data using the estimated slope of symptoms from the model or using last value carried forward. The later is unlikely to arise in practice for an acute infection, however provides a useful extreme bound in which to interpret results.

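### The first symptom score comes after the consultation in which both interventions act, and the effect is read from slopes, so an early difference can be missed or look like slower recovery

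*Protocol article*

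**What the plan says.** All references are to the Protocol article.

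- **When the interventions act.** CRP point of care test: "CRP analysis will be carried out during the consultation". Under the seminar on shared decision making, trained GPs are asked to "implement the specific steps of the communication training in their routine acute cough consultations". Both exposures therefore fall within the index consultation.
- **When symptoms are scored.** Data collection: "The practice nurse will give each participant a simple self-complete symptom diary after the consultation". The diary opens with questions that include the consultation itself: "After general questions on cough and the consultation, patients will be asked each day". The score is daily: "patients will be asked each day to complete a 6 item scale, with responses to statements ranging from 0 to 6", so the total runs from 0 to 36.
- **What is recorded at the consultation.** The text says only that "the GP will take written consent and note the inclusion criteria on the trial inclusion form".
- **How recovery is analysed.** "The clinical effectiveness analysis will be based on diary responses". The Analysis section fits a four-level linear model to the logged scores and states: "The effect of interventions would be seen in the comparison of the slopes of symptom scores over time in the groups". It interprets these slopes as quicker or slower recovery.
- **Baseline.** The Discussion warns of recruitment bias after randomisation. It answers with monitoring of recruitment rates and a description of baseline characteristics.

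**The concern.** A comparison of slopes asks how fast each group moves away from its own first score. It gives no credit for where that first score lies. In this trial a difference at the first score has two plausible sources:

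1. **An early effect.** The trial is open, and the Background expects a low CRP result to reassure the patient. Some of the six self-rated items (sleep, daily activities, feeling unwell) could respond to reassurance before the first diary entry.
2. **Different severity at entry.** Practices are randomised before patients are recruited, and only 20 practices take part. GPs in one group may enrol milder patients. This route needs no rapid effect of reassurance.

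Without a score from before the consultation, the two cannot be told apart. The Background describes acute bronchitis as usually self-limiting, so some convergence of the groups is to be expected. If that convergence also holds on the log scale, the group that began lower has the flatter slope.

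Clinical recovery is the first secondary outcome listed. The Abstract presents the communication training as a way to cut prescribing at no cost to recovery, and the Discussion makes wider use conditional on good clinical outcomes. A measure that can overlook a benefit, or show it as a delay, weakens that reassurance.

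**Working it through.** The article gives no mean, SD, slope or power for the symptom score, so there is no stated figure to reproduce. The check shows what a slope comparison does with a difference already present at the first score. **All scores below are assumptions.**

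**General form.** Let d(t) be the difference in mean log score (intervention minus control) t days after the first entry. With straight lines on the log scale, d(t) = d(0) + Δ·t, where Δ is the slope difference.

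- If the proportional difference persists, d(t) = d(0) throughout and Δ = 0.
- If the groups meet at time T, Δ = −d(0)/T. When d(0) is negative (intervention lower at the start), Δ is positive, which is a flatter slope.

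**Endpoint example.** Control scores 18 on diary day 1 and 2 on day 28, so T = 27.

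- Control: (ln 18 − ln 2)/27 = 0.0814 per day.
- Intervention starting at 16 and ending at 2: (ln 16 − ln 2)/27 = 0.0770. Ratio 0.946, about 5% slower.
- Intervention starting at 15 and ending at 2: (ln 15 − ln 2)/27 = 0.0746. Ratio 0.917, about 8% slower.

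The average log difference over the period is d(0)/2:

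- From 16: ln(16/18)/2 = −0.059, a geometric mean score about 6% lower.
- From 15: ln(15/18)/2 = −0.091, about 9% lower.

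Level and slope therefore point in opposite directions, although the intervention group is never worse.

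**The same starts without convergence on the log scale.** If 16 falls at the control rate, it ends at 2 × 16/18 = 1.78; if 15 does, it ends at 2 × 15/18 = 1.67. The slope difference is then zero. Final gaps of only 0.22 and 0.33 points on a 0–36 scale separate a missed difference from a reversed one.

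**Other shapes of benefit.** Control score 20·exp(−0.08t) from the first entry, with a least-squares line through the daily log scores. The control slope is −0.0800. A positive Δ reads as slower recovery.

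| Assumed pattern in the intervention group | Δ, 14 days | Δ, 28 days | Reading |
|---|---|---|---|
| 20% lower at first score, waning with a 5-day half-life | +0.0138 | +0.0066 | slower |
| 20% lower at first score, waning linearly to zero | +0.0171 | +0.0083 | slower |
| 20% lower at first score, persisting | 0.0000 | 0.0000 | no difference |
| Builds to 20% over the first three diary days, persists | −0.0092 | −0.0025 | faster |
| Constant 3 points lower (floor 0.5) | −0.0290 | −0.0693 | faster |

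In every row the intervention group has the lower mean score over the period. In the first row, for example, it is 1.39 points lower over 14 days and 0.73 lower over 28.

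**The case against.** **Reversal is not inevitable.** A reader might infer that any early benefit will show up as slower recovery. The documents do not support that. The model works on logged scores, and two groups falling at the same proportional rate have equal slopes even though their raw scores converge towards zero. A benefit that builds after the first entry and persists, or one that is constant in points, gives a steeper slope. This objection stands and limits the point to what can happen.

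**The size is unknown.** Nothing in the article shows how far reassurance moves the score before the first diary entry. Three of the six items are cough, phlegm and breathlessness, which may hardly move. A reader might also want to know whether such a slope difference would be statistically detectable. The article gives no variance for the score, and any standard error would have to allow for clustering by practice, so no such claim is made here. This stands too.

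**A baseline may exist, and level terms may be reported.** A reader might infer that no symptom record precedes exposure and that group level is left out of the model. Neither can be established. Figure 1 and the inclusion form are not shown. The GP notes inclusion criteria that involve signs and symptoms, and further model detail may lie in a fuller document. What remains is that the diary is the stated basis of the clinical analysis, and that the slope comparison is the only effect measure the article names for this score.

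**The slope has a virtue.** On the log scale it is unaffected by a proportional difference in severity at entry that persists. An unadjusted comparison of levels is not. This stands and shapes the fix.

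**Other recovery data are collected**, namely return to usual activities, time off work and re-consultation. That softens the consequence but does not change how the symptom score is read.

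**Conclusion.** The point holds in a conditional form. The symptom score is first described as taken after exposure to both interventions, and its effect is read from slopes of the logged score. A difference present at the first entry is missed if it stays proportional, and can look like slower recovery if the groups converge on the log scale.

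Under the assumed scores, convergence makes the better group look about 5% to 8% slower in the endpoint example. With an assumed 20% early benefit that wanes, the slope difference is about +0.007 to +0.017 per day. These figures illustrate the direction and rough scale; they are not predictions for this trial. Without a score from before the consultation, an early effect also cannot be separated from imbalance at entry.

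Only a secondary outcome is affected; the primary outcome, prescribing at the index consultation, is not. The change is worth making because the claim of unharmed recovery leans on this analysis.

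**What to change.** 1. **Baseline score.** Have the patient score the same six items at consent, before the CRP test and before management is discussed, unless the inclusion form already records this. Use that score as a covariate in the symptom model.
2. **Effect measure.** Report the baseline-adjusted difference in mean log score over days 1–28 together with the slope difference. Test the intervention main effect and the intervention-by-time term jointly. State that a flatter slope will not by itself be read as slower recovery.
3. **If no score before the consultation is collected.** Report level alongside slope, but do not replace the slope with it. An unadjusted level difference would carry any imbalance in severity at entry, which the Discussion itself warns about.

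The cost is one short extra form per patient and a sentence or two in the Analysis section. The downside is that the baseline is completed in the practice while later scores are self-completed in the diary, so the setting differs. Having the patient complete it before any discussion limits the GP's influence on it.
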